### 2.2 Selection of subjects

#### 2.2.1 Sample size estimation

When calculating the sample size for the upcoming project on selective screening, we relied on published similar studies. Researchers pointed out the following essential factors contributing to the sample size calculation: Daniel’s formula for prevalence studies in case of expanded screenings, the reported frequencies of different IEM within the studied populations, and the number of infants born in the country during the period of interest (Yoon et al., 2005; Golbahar et al., 2013; Hassan et al., 2016; Shibata et al., 2018; Sarker et al., 2019; Manta-Vogli et al., 2020). Notably, many researchers corrected their calculations, considering the situation with consanguineous marriages in their country.

According to the review by Shibata N et al., the IEM overall detection frequency was 3.0% (1.2% in Japan and 9.2% in other Asian countries) (Shibata et al., 2018). Yoon et al. reported 5.4% IEM among South Korean annual births (Yoon et al., 2005). Of these data on IEM frequency throughout Asian countries, Mongolian values (1.6%) have attracted our attention due to the similar nomadic history and way of life where consanguineous marriages were strictly forbidden (Shibata et al., 2018). Along with that, the Mongolian index does not include all types of IEM except the most distributed.

Based on mentioned factors, we requested data on the number of childbirths across the four provinces (oblasts) of western Kazakhstan within 3 years before the project started. The average rate of infants born alive annually ranged between 69–73,000 (https://stat.gov.kz/en/industries/social-statistics/demography/publications/). Thus, we have decided to build on the IEM average frequency of 2%–2.5% and determined the expected sample size of 1,500 children for selective screening with 750 healthy controls.

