#### 2.2.2 Study population. inclusion and exclusion criteria

In this research, we are consecutively recruiting a sample of eligible 2,250 children across the region (1,500 children aged 1 day to 18 years suspected of IEM and 750 healthy children to set the reference values). Western Kazakhstan is divided into four regions (provinces, oblasts) according to the administrative division: Aktobe, West Kazakhstan, Atyrau, and Mangystau (Figure 2).

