Indices of sensitivity (Sn), specificity (Sp), positive predictive values (PPVs), and negative predictive values (PVN) will be calculated for each diagnostic test under consideration. PPVs will be calculated by dividing the total number of true positive cases by the total number of true positive and false positive cases. The detection rate will be calculated by dividing the number of cases diagnosed by the number of screened children with suspected metabolic disorders. Multiple linear regression coefficients will be calculated to assess the relationship of each analyte with the factors of gender, weight, and place of residence. Due to the number of variables subjected to analysis, and the anticipated presence of multiple outcomes, the included tests may not be sufficient. So, the cluster analysis and, possibly, the decision-tree method will be applied. Decision trees break down complex data into more manageable parts, beneficial in prediction analysis, data classification, and regression. A dimensionality reduction method, principal component analysis (PCA), will also be applied. Two-sided levels <0.05 are assumed to be statistically significant. Statistical analysis will be carried out using the statistical packages IBM SPSS v. 23.0 (IBM, Armonk, NY, United States), Statistica (StatSoft, Inc., Tulsa, OK, United States, v. 10), and R 3.3.2 (R Foundation for Statistical Computing, Vienna, Austria.)

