### 3.3 Presenting detected cases

The results of LC-MS/MS in affected individuals will be presented as metabolic profiles. The metabolic profile of each affected individual will be placed next to the metabolic profile of a healthy individual from the control group, corresponding to gender, age, and place of residence. IEMs detected, their frequency, primary clinical manifestations, and main diagnostic markers in high-risk children confirmed by LC-MS/MS will be described in the tables. The average age of patients at the time of diagnosis will also be recorded. Table 4 displays the most common clinical manifestations in patients diagnosed with IEM. This list can be expanded by the results obtained in the study.

**TABLE 4 T4:** Common features encountered in children with different IEM (N = ***).

Variables	Number of patients (percent)
Developmental delay	
Neurological abnormalities	
Disturbed consciousness level	
Vomiting/dehydration	
Hyperammonemia	
Metabolic acidosis	
MRI brain abnormalities	
Infections	
Hypoglycemia	
Mental retardation	
Organomegaly	
Micro/macrocephaly	
Ophthalmic abnormalities	
Cardiomyopathy	
Seizures	
Tachypnea	
Thrombocytopenia	
Abnormal smell	
Hair growth disorders	
Osteoarticular anomalies	
Abnormal muscle tone	
Mutism	
Dysmorphia	

The baseline and repeated LC-MS/MS analysis results and biochemical confirmation in children diagnosed with IEM, according to the diagnosed disease, will also be presented. Demographic and laboratory data of confirmed cases detected by LC-MS/MS among 1,500 Kazakhstani children with suspected IEM will be presented in Table 5. Also, the table will include data on the reference values of the considered metabolites obtained in a sample of healthy controls.

**TABLE 5 T5:** Cases detected by LC-MS/MS among 1,500 children suspected IEM.

Metabolic disorder	Metabolite detected by LC- MS/MS (Abnormal parameter)	Positive cases, n (%)	Concentration mean (range) (μmol/L)	Cut-off limit (μmol/L)	References range (μmol/L)	Province (oblast), positive cases (n)
						
						

IEM, identified by selective screening with calculated frequencies for each disease, will be described separately for diseases belonging to the AAD, OA, and FAOD groups.

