### 3.4 Presenting IEM frequencies in the child population

The frequency of inborn errors of metabolism detected using tandem mass spectrometry, depending on the geographical location and type of IEM in western Kazakhstan during the period from 2023 to 2024, can be represented graphically in the form of accumulation diagrams demonstrating the contribution of AAD, OA, and FAOD to the total incidence of IEM. Also, these data can be presented in the form of a table. The data will include the total number of IEM cases in the high-risk group of children and the absolute number and frequency of cases for each identified disease. Detection rates for selective screening and incidence will be calculated according to the number of children born in western Kazakhstan during the study period, in 2023–2024, for each specific disease. These data will allow for estimating the number of affected male and female children and determining which IEMs were the most common in the studied population. Given that selective screening of the child population in western Kazakhstan will be carried out for about 2 years (2023–2024, recruitment of high-risk children), the incidence rate for each class of disorders (AAD, OA, FAOD) will be established, taking into account the total number of births each year.

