Thus, the number of IEMs to be included in the protocol of the future ENBS in Kazakhstan through LC-MS/MS will depend, in addition to economic factors and laboratory equipment, on the frequency of diseases established during selective screening. In describing established cases of IEM, in addition to presenting the data specified in the Results section, the present study implies reflecting the family history of IEM, including the number of patients and families with IEM, gender, positive family history, consanguineous marriages, and age of the symptoms onset. Although, due to the historically and socially established forbiddance for consanguineous marriages in Kazakhstan, we assume their rare prevalence, the data obtained would be of interest for comparison with populations for which similar results are already available (Guthrie and Susi, 1963; Al Riyami et al., 2012; Golbahar et al., 2013; Hassan et al., 2016; Gayduk et al., 2022).

In the present study, the distribution of IEM primary clinical symptoms and their severity will be analyzed by age. Delayed diagnosis at an older age is commonly associated with many severe and irreversible clinical complications in patients (Champion, 2010; Selim et al., 2014; Han et al., 2015; Lampret et al., 2015; Dietzen et al., 2016). This circumstance calls for the urgent need for early detection and intervention to achieve favorable outcomes in IEM.

• Study limitations.1. The number of children with clinical manifestations to be examined in the ongoing screening for IEM by LC-MS/MS is limited.2. Other parts of Kazakhstan are not involved in the study. As such, assessing the differences between the levels of AAs, ACs, and SuAc in DBS of the child population and the differences in the IEM incidence appear impossible.3. The need for multiple and expensive tests to rule out rare and ultra-rare IEM.4. Metabolites for diagnosing other hereditary metabolic diseases, such as disorders of carbohydrate metabolism, disorders of porphyrin metabolism, disorders of purine and pyrimidine metabolism, disorders of steroid metabolism, disorders of mitochondrial function, disorders of peroxisomal function, and lysosomal storage disorders, are not included in this study.

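### The planned incidence per birth is the detection rate multiplied by the number screened over births, so its absolute level depends on how many children are screened as well as on disease frequency

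*Protocol article*

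**What the plan says.** **Number screened.** Section 2.2.1 of the protocol article "determined the expected sample size of 1,500 children for selective screening with 750 healthy controls". Section 2.2.2 adds that "we are consecutively recruiting a sample of eligible 2,250 children across the region", through 7 pediatric hospitals. The results table in section 3.3 is already titled "Cases detected by LC-MS/MS among 1,500 children suspected IEM".

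**Detection rate.** Section 3.2: "The detection rate will be calculated by dividing the number of cases diagnosed by the number of screened children with suspected metabolic disorders".

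**Incidence.** Sections 3.4 and 4 also relate the cases to children born in the region in 2023–2024, disease by disease. For the three classes (amino acid disorders, AAD; organic acidemias, OA; fatty acid oxidation disorders, FAOD), section 3.4 states that "the incidence rate for each class of disorders (AAD, OA, FAOD) will be established, taking into account the total number of births each year". Section 4 then plans to match the frequency of each disorder with incidence data from other parts of the world.

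**Caveats.** Section 4 says that a thorough assessment of prevalence would need expanded newborn screening, which is not affordable at present, and that selective screening can support relative frequencies. Its limitations list includes: "The number of children with clinical manifestations to be examined in the ongoing screening for IEM by LC-MS/MS is limited". Neither remark is tied to the incidence figure, and that analysis stays in the plan.

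**The concern.** An incidence over all births in a region needs a numerator that contains all the cases arising there, or a correction for those that were missed. Here the numerator is the cases found among a planned number of referred, symptomatic children. The protocol does not say that these are all the eligible children in the four provinces, and it does not plan to count eligible children who were not screened. The ratio therefore contains a factor, children screened per birth, that comes from recruitment and not from biology.

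This matters because of how the figure will be used. The hypothesis in section 1 is that frequencies will be lower than in countries where consanguineous marriage is customary, and section 4 plans the international comparison. If eligible children outnumber those screened, the shortfall pushes the figure down, which is the direction of the hypothesis. A low value could then be taken as support when it partly reflects enrolment. Section 4 also says that the frequencies found will help decide which disorders enter a future national newborn programme.

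**Working it through.** The protocol gives no expected incidence, so there is no stated figure to reproduce. The check uses its definitions and planning inputs.

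**Inputs**
- Number screened: 1,500 (sections 2.2.1, 2.2.2 and 3.3).
- Planning frequency: "we have decided to build on the IEM average frequency of 2%–2.5" per cent (section 2.2.1), taken here as the detection rate among screened children. This is an assumption.
- Births: "The average rate of infants born alive annually ranged between 69–73,000" (section 2.2.1). Assuming that this holds in 2023–2024, two years give 2 × 69,000 = 138,000 to 2 × 73,000 = 146,000.

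**Step 1: the identity**

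cases / births = (cases / screened) × (screened / births) = detection rate × (screened / births)

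The second factor is 1,500 / 146,000 = 10.3 to 1,500 / 138,000 = 10.9 children screened per 1,000 births.

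**Step 2: the figure as planned**
- Low end: 0.02 × 1,500 = 30 cases; 30 / 146,000 = 20.5 per 100,000.
- High end: 0.025 × 1,500 = 37.5 cases; 37.5 / 138,000 = 27.2 per 100,000.

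**Step 3: change the number screened, hold the detection rate**

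| Screened | Cases at 2–2.5% | Per 100,000 births |
|---|---|---|
| 750 | 15–18.75 | 10.3–13.6 |
| 1,500 | 30–37.5 | 20.5–27.2 |
| 3,000 | 60–75 | 41.1–54.3 |

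The figure is exactly proportional to enrolment. The constant detection rate is an assumption, because the protocol gives no count of eligible children.

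**Step 4: hold 1,500 screened, change the detection rate** (142,000 births, the midpoint)
- 1%: 15 / 142,000 = 10.6 per 100,000
- 2%: 30 / 142,000 = 21.1
- 3%: 45 / 142,000 = 31.7

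The figure therefore also follows disease frequency.

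**Step 5: both effects together** (illustrative pool sizes, 142,000 births)

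Suppose that 3,000 children are eligible and 60 of them have an IEM (inborn error of metabolism). Screening 1,500 of them finds about 1,500 × 60 / 3,000 = 30 cases. The reported figure is 21.1 per 100,000, against 60 / 142,000 = 42.3 in the whole pool. Keep the 2,940 unaffected eligible children and let the true cases be 30, 60 or 120:
- 1,500 × 30 / 2,970 = 15.2 cases, reported 10.7, whole pool 21.1
- 1,500 × 60 / 3,000 = 30.0 cases, reported 21.1, whole pool 42.3
- 1,500 × 120 / 3,060 = 58.8 cases, reported 41.4, whole pool 84.5

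The reported figure tracks the disease, but at about half its level, because about half the pool was screened.

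**Step 6: class shares**

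For any class, (class cases / births) / (all cases / births) = class cases / all cases. The births and the number screened both cancel, so the relative contributions of AAD, OA and FAOD do not depend on the factor in Step 1.

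**The case against.** The strongest reply has four parts.

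1. **No stopping rule is stated.** The 1,500 is called an expected size, recruitment is consecutive, and data collection has a calendar end in August 2024. If the calendar governs, the number screened reflects referral volume. This stands against treating 1,500 as a hard cap: the text does not say that eligible children would be turned away. It does not remove the problem, because the identity holds for whatever number is screened and completeness is still not claimed.

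2. **The figure does carry information about disease.** A reader might infer that it moves with the enrolment target and not with disease frequency. Step 4 shows otherwise: at fixed enrolment it is proportional to the detection rate. Only its absolute level is uninterpretable without the screened fraction.

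3. **The halving and doubling are conditional.** If the seven hospitals already see nearly every suspected case, enrolling more children would not find proportionally more disease. This is fair. The true distortion is unknown, and the 750 and 3,000 scenarios show sensitivity, not a forecast.

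4. **The protocol discloses the limits.** Section 4 says that this is selective screening only, that prevalence proper needs newborn screening, and that the number examined is limited. These statements soften the claim, but the incidence wording and the international comparison remain.

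A reader might also suppose that the 1,500 was set by budget. Section 2.2.1 bases it on published frequencies and regional births; the financing remark in section 4 concerns expanded newborn screening.

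**Conclusion.** The point holds in a limited form. The planned per-birth incidence equals the detection rate times children screened per birth. Its absolute level therefore depends on enrolment as well as on disease frequency, and it cannot serve as population incidence or be compared with incidence elsewhere. On the planning inputs it would be 20.5–27.2 per 100,000 births, with 10.3–10.9 children screened per 1,000 births. This assumes a 2–2.5% detection rate, 1,500 screened and two years at 69,000–73,000 births. The relative shares of AAD, OA and FAOD are not affected, nor is the detection rate per screened child.

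It is tempting to call the per-birth figure a lower bound. The protocol does not support that as it stands. Children up to 18 years are enrolled (section 2.2.4), while the denominator is births in 2023–2024 only (section 3.4). Cases from earlier birth years can enter the numerator and push the ratio up, against the downward effect of incomplete screening. The net direction is not known.

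**What to change.** In sections 3.4 and 4:

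- Make the detection rate per screened child, with a confidence interval, the main frequency. With 1,500 screened, the normal-approximation 95% half-width, 1.96 × √(p(1 − p)/1,500), is 0.71 percentage points at 2% and 0.79 at 2.5%.
- Compare that rate only with other selective-screening studies. Sections 2.2.1 and 4 already cite detection rates of this kind.
- Rename the per-birth figure *detected cases per 100,000 births* and print the number screened per 1,000 births beside it.
- Do not match it with incidence from whole-population screening.
- Call it a lower bound only if the numerator is restricted to children born in the denominator years.

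The cost is rewording two sections and adding one table column and a confidence interval. No extra data are needed unless the lower-bound label is wanted, which requires selecting cases by birth year. The downside is a weaker headline: the study would report how often disease is found among referred children, not the regional incidence.

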### 3.5 Presenting positive and false positive cases

Even though the number of false positive results during LC-MS/MS is much lower than when using standard biochemical tests and, according to different researchers, ranges from 1.9% to 2.3% (Selim et al., 2014; Hassan et al., 2016), we assume that a certain number of samples will turn out to be a false positive. The number of true and false positives for each disease according to each disorder after the primary (baseline) LC-MS/MS will be established. Positive predictive values will be calculated by the total number of true positive cases divided by the total number of true positive and false positive cases.

## 4 Discussion

The present study assumes only selective screening for IEM. Implementing ENBS, which allows for thoroughly assessing the prevalence of IEM in the child population of western Kazakhstan, is currently unavailable due to a lack of proper financing. In addition, given that the overall prevalence of IEM in populations is relatively low, less than 1:100,000 for most of them, coverage for expanded newborn screening should be total. Besides, it is known that not all IEMs are diagnosed during ENBS, as some disorders debut at a later age (Hassan et al., 2016). Nonetheless, the data of selective screening conducted among children at high risk of IEM, given the inclusion in the study of the largest pediatric hospitals in western Kazakhstan, can serve as a basis for calculating the relative frequencies of various IEMs in the child population of the region.

Detection rates for selective screening and incidence will be calculated according to the number of children born alive in the region during the study period, in 2023–2024, for each specific disease. These data will allow for estimating the number of affected male and female children and determining which IEMs are the most common. The frequencies of each IEM revealed across the child population of western Kazakhstan will be matched with incidence data in other regions of the world.

Conducting ENBS and selective screening for IEM in Kazakhstan is of particular interest due to the entire absence of similar studies in the region of Central Asia, despite a significant number of studies conducted in neighboring areas (Russia, China, India, the Middle East, countries of East and Southeast Asia) (Guthrie and Susi, 1963; Nagaraja et al., 2010; Shibata et al., 2018; Therrell and Padilla, 2018; Yang et al., 2020; Deng et al., 2021; Loeber et al., 2021). A study by Shibata et al. revealed different rates of IEM incidence and spectrum of diseases in Asian countries. In addition, it was found that the ranges of IEM diseases determined using selective screening differed from those detected using ENBS (Shibata et al., 2018). For instance, the incidence of phenylketonuria in Asians (∼1:50,000 in Korea; ∼1:110,000 in Japan) is much lower than in Caucasians (∼1:10,000). The medium-chain acyl-CoA dehydrogenase (MCAD) deficiency, a common genetic metabolic disorder in Caucasian children with the A985G mutation of frequent occurrence, can serve as another example. Unlike Caucasians, MCAD is extremely rare in Korea and Japan (Vieira Neto et al., 2012). The frequencies (specific contribution to the IEM spectrum) of FAOD in the United States newborn population are, according to various studies, 45.2% in North Carolina (Frazier et al., 2006) and 38% in California (Feuchtbaum et al., 2012), which is slightly higher than in some European countries (Lindner et al., 2011; Shibata et al., 2018) and much exceeds the frequency of FAOD in Asian countries (Guthrie and Susi, 1963; Golbahar et al., 2013; Selim et al., 2014; Hassan et al., 2016; Shibata et al., 2018). FAOD detection rates for selective screening vary across countries, ranging from 0.29% in a South Korean study (Yoon et al., 2005) to 10.8% in a study in Oman (Al Riyami et al., 2012).

Thus, the number of IEMs to be included in the protocol of the future ENBS in Kazakhstan through LC-MS/MS will depend, in addition to economic factors and laboratory equipment, on the frequency of diseases established during selective screening. In describing established cases of IEM, in addition to presenting the data specified in the Results section, the present study implies reflecting the family history of IEM, including the number of patients and families with IEM, gender, positive family history, consanguineous marriages, and age of the symptoms onset. Although, due to the historically and socially established forbiddance for consanguineous marriages in Kazakhstan, we assume their rare prevalence, the data obtained would be of interest for comparison with populations for which similar results are already available (Guthrie and Susi, 1963; Al Riyami et al., 2012; Golbahar et al., 2013; Hassan et al., 2016; Gayduk et al., 2022).

In the present study, the distribution of IEM primary clinical symptoms and their severity will be analyzed by age. Delayed diagnosis at an older age is commonly associated with many severe and irreversible clinical complications in patients (Champion, 2010; Selim et al., 2014; Han et al., 2015; Lampret et al., 2015; Dietzen et al., 2016). This circumstance calls for the urgent need for early detection and intervention to achieve favorable outcomes in IEM.

• Study limitations.1. The number of children with clinical manifestations to be examined in the ongoing screening for IEM by LC-MS/MS is limited.2. Other parts of Kazakhstan are not involved in the study. As such, assessing the differences between the levels of AAs, ACs, and SuAc in DBS of the child population and the differences in the IEM incidence appear impossible.3. The need for multiple and expensive tests to rule out rare and ultra-rare IEM.4. Metabolites for diagnosing other hereditary metabolic diseases, such as disorders of carbohydrate metabolism, disorders of porphyrin metabolism, disorders of purine and pyrimidine metabolism, disorders of steroid metabolism, disorders of mitochondrial function, disorders of peroxisomal function, and lysosomal storage disorders, are not included in this study.

As such, this study is the first in Kazakhstan and Central Asia to assess the prevalence of IEM among children at risk. Also, reference values of metabolites for three different age groups of the child population in western Kazakhstan will be established for the first time. Our research can be considered a pilot and expected to give an impulse to launch a nationwide ENBS program using LC-MS/MS. Overall, the study will further develop the national as selective as expanded newborn screening programs.

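### Read literally, sections 3.4 and 4 put the selective-screening detection rate on regional births, against the per-child-screened definition in section 3.2

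*Protocol article*

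**What the plan says.** The protocol article gives one explicit formula. Section 3.2 (Statistical analysis) states: "The detection rate will be calculated by dividing the number of cases diagnosed by the number of screened children with suspected metabolic disorders".

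Two later sentences use a different base. Section 3.4 states: "Detection rates for selective screening and incidence will be calculated according to the number of children born in western Kazakhstan during the study period", which it dates to 2023–2024. Section 4 (Discussion) repeats this almost word for word: "Detection rates for selective screening and incidence will be calculated according to the number of children born alive in the region". In both, detection rates and incidence are joint subjects of one clause, and births are the only base named.

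Section 3.4 closes by saying that an incidence rate for each class of disorder will take account of each year's births. That sentence does not mention detection rates.

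**The concern.** One named quantity has two denominators. An analyst who follows section 3.2 reports a percentage of referred, suspected children. One who follows the births sentence in section 3.4 or 4 reports a fraction of all regional births under the same name.

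The scale matters because task 3 is comparison with published reports from other populations, and the selective-screening figures the article quotes are percentages: "FAOD detection rates for selective screening vary across countries, ranging from 0.29% in a South Korean study" up to 10.8% in a study in Oman. A per-birth number labelled a detection rate could not be set beside them.

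The births sentence raises a second question. Participants may be up to 18 years old, so many detected cases may not belong to the 2023–2024 births over which they would be divided.

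**Working it through.** **Inputs**

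- Children to be screened: 1,500, at an expected frequency of 2%–2.5% (section 2.2.1: "we have decided to build on the IEM average frequency of 2%–2.5% and determined the expected sample size of 1,500 children for selective screening").
- Births: section 2.2.1 says "The average rate of infants born alive annually ranged between 69–73,000", i.e. 69,000 to 73,000 a year in the four provinces before the project.
- Birth window: section 3.4 describes screening as "carried out for about 2 years (2023–2024, recruitment of high-risk children", which gives 24 months. Section 2.1 ends data collection in August 2024, which gives 20 months if births are counted from January 2023. The document does not settle this, so both are shown.

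The article states no ratio of the two denominators, so there is no figure of its own to reproduce. It also states no precision target behind the 1,500. The point does not depend on how that number was reached.

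**Ratio of denominators** = (annual births × months / 12) / 1,500

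| Window | Births | Ratio |
|---|---|---|
| 24 months | 2 × 69,000 = 138,000 to 2 × 73,000 = 146,000 | 92.0 to 97.3 |
| 20 months | 69,000 × 20/12 = 115,000 to 73,000 × 20/12 = 121,667 | 76.7 to 81.1 |

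**The same cases on each base**

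- Expected cases: 2% × 1,500 = 30; 2.5% × 1,500 = 37.5.
- Section 3.2 base: 30 / 1,500 = 2.0%.
- Births base, 24 months: 30 / 146,000 = 0.0205% to 30 / 138,000 = 0.0217%.
- Births base, 20 months: 30 / 121,667 = 0.0247% to 30 / 115,000 = 0.0261%.

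The births base therefore gives about 0.021% to 0.026%.

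**Which base the rest of the article fits**

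- The sizing frequency of 2%–2.5% is paired with 1,500 children for selective screening.
- Table 5 (section 3.3) reports positive cases as n (%) among the 1,500 suspected children.
- Section 2.3.5 assesses the 37 disorders in a group of children at high risk.
- The fatty acid oxidation comparators in section 4 (0.29% to 10.8%) are called selective-screening detection rates.
- Section 4 puts most of these disorders below 1 in 100,000. Even 37 disorders all at that ceiling would sum to 37 / 100,000 = 0.037%. A few commoner disorders would raise this, but not plausibly to 2%.

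All of these agree with section 3.2. Only the births sentence, in its two places, does not.

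**The case against.** The strongest reply is that the article already answers the question. Section 3.2 is the analysis section and has the only division formula. Sections 3.4 and 4 speak loosely of calculating according to births, and the end of section 3.4 ties births to incidence. On that reading, two quantities were joined carelessly in one sentence, and births were meant for the second alone. As an account of intent this is probably right. It does not remove the conflict: the sentence appears twice, and neither place limits births to incidence.

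A reader might infer more than the document supports:

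- **That the study's main result is undefined.** Section 3.1 does not list the detection rate as a primary outcome. The second primary outcome is a number and proportion of children with abnormal metabolite values.
- **That the region will be made to look almost free of these disorders, as the research hypothesis predicts.** This would require a per-birth figure to be compared with per-screened percentages. No section plans that. Section 4 says the population frequencies will be matched with incidence data elsewhere, which is like with like.
- **That the discrepancy is about 95-fold.** That holds only for two full calendar years of births.

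A further caution stands. Section 2.2.1 quotes 5.4% from the South Korean study as a share of annual births, while section 4 cites the same study for a selective-screening rate. The base that study used cannot be checked from the article, so the fit of the comparators to section 3.2 is strong but not proven for every figure.

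**Conclusion.** The point holds as an inconsistency in the current text. Section 3.2 puts the detection rate on children screened; sections 3.4 and 4, taken literally, put it on regional births. The surrounding material favours section 3.2.

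The two bases differ about 77- to 97-fold. This assumes that all 1,500 children are screened, that births stay at 69,000–73,000 a year, and that births are counted over 20 to 24 months. The size of the ratio shows that the two quantities cannot share a name. It does not show that a biased comparison is planned, and the document does not support that inference.

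The correction is worth making because following either births sentence as written would produce a wrongly labelled rate. A births-based incidence also needs its own numerator rule, given the age range of participants.

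**What to change.** 1. In the births sentence of section 3.4 and its repeat in section 4, strike the opening words that name detection rates, so that incidence is the only quantity calculated on births.
2. In both places, refer to section 3.2 for the detection rate: confirmed cases over children screened. Say that only this rate is compared with other selective-screening programmes.
3. Name the births-based quantity separately as incidence. Limit its numerator to cases born in the same 2023–2024 period as the denominator, and state the months of births counted.

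The first two changes are wording in two sentences. The third adds one definition and should need no new data, since age is already collected (Table 1). Sample size and laboratory procedures are unaffected.
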